## ELIGIBILITY CRITERIA

4

### Inclusion criteria

4.1

Each participant must meet all of the following inclusion criteria to be enrolled in either the two cohorts within the study:Willing and able to provide written informed consentMale sexAge ≥ 16 yearsHistologically confirmed seminoma or NSGCT (biopsy/orchidectomy)International Germ Cell Cancer Collaborative Group (IGCCCG) good prognosis groupClinical stage II (standard of care cross‐sectional imaging) at time of study entryAbility to comply with the protocol, including but not limited to, completion of the patient‐reported outcome questionnairesECOG performance status 0–1

#### rRPLND de‐escalation group specific inclusion criteria

4.1.1

Participants must meet the following additional inclusion criteria:Histologically confirmed seminoma (biopsy/orchidectomy).Stage IIA and <3 cm IIB with ipsilateral lymph node(s) within rRPLND template.Negative or mildly elevated serum tumour markers, defined as:AFP (alpha‐fetoprotein) within normal range or <20 ng/ml if stable on at least two serial measurements.BhCG (human chorionic gonadotropin) < 50 mg/ml.LDH (lactate dehydrogenase) < 1.5x upper limit normal.
Fit for surgery, defined as meeting all of the following criteria:Body mass index (BMI) not expected to preclude surgery as assessed by the investigator.Charlson comorbidity index ≤3.No significant cardio‐pulmonary disease, or other uncontrolled intercurrent illness that would limit fitness for surgery in the opinion of the investigator.

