#### Carboplatin AUC10 de‐escalation group‐specific inclusion criteria

4.1.2

Participants must meet the following additional inclusion criteria:Histologically confirmed seminoma (biopsy/orchidectomy).Serum tumour markers, defined by IGCCCG good prognosis criteria:AFP < 10 ng/ml and non‐rising on serial testing.Any BhCG.LDH < 2.5x ULN.
Glomerular filtration rate by EDTA clearance over 25 ml/min (a measured creatinine clearance using Cockcroft and Gault would be allowed if unable to perform EDTA clearance).Participants must be sterile or agree to use adequate contraception during the period of therapy.

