### Intervention

5.1

Participants will receive SOC treatments for good prognosis stage II seminoma and NSGCT or de‐escalated treatments (primary rRPLND with or without adjuvant treatment or Carboplatin AUC10) for stage II seminoma. Participants will be allocated to one of the following two cohorts based on whether the relevant de‐escalated treatment is adopted as an institutional SOC:rRPLND cohort: Participants with ipsilateral stage IIA or <3 cm IIB seminoma with negative/low for tumour markers will be offered rRPLND followed by adjuvant treatment or surveillance based on post‐operative histology as per institutional SOC.Carboplatin AUC10 cohort: Participants with stage II seminoma will be offered Carboplatin AUC10 by 3 cycles.

Participants deemed ineligible for Carboplatin AUC10 or rRPLND or those who decline this de‐escalation option will be offered either BEP or EP chemotherapy (seminoma and NSGCT) or radiotherapy with or without neoadjuvant Carboplatin AUC7 (seminoma) and will continue to be followed in the study. Chemotherapy treatment strategies and adjuvant treatments are left to the shared decision‐making between treating clinicians and participants and follow institutional SOC. The study flow diagram outlining the treatment cohorts is summarised in Figure 1.

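### The BhCG limit for the rRPLND group is printed in mg/ml, so as a number it excludes nobody and contradicts the low-marker restriction it is meant to define

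*Protocol article*

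**What the plan says.** Section 4.1.1 of the protocol article lists the extra criteria for the rRPLND de-escalation group. The marker criterion opens with "Negative or mildly elevated serum tumour markers, defined as" and then gives three limits:

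- "AFP (alpha‐fetoprotein) within normal range or <20 ng/ml if stable on at least two serial measurements"
- "BhCG (human chorionic gonadotropin) < 50 mg/ml"
- "LDH (lactate dehydrogenase) < 1.5x upper limit normal"

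Section 5.1 (Intervention) repeats the restriction in words: "Participants with ipsilateral stage IIA or <3 cm IIB seminoma with negative/low for tumour markers will be offered rRPLND".

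Section 4.1.2, for the Carboplatin AUC10 group, sets an AFP limit ("AFP < 10 ng/ml and non‐rising on serial testing") and an LDH limit but accepts any BhCG. No other part of the article gives a BhCG limit or a BhCG unit.

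**The concern.** The lead-in and section 5.1 both say that only patients with normal or slightly raised markers should be offered rRPLND. A BhCG limit in milligrams per millilitre cannot express that. AFP, the neighbouring protein marker, is limited in nanograms per millilitre, a unit one million times smaller.

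The contrast with section 4.1.2 shows that the limit was meant to select. Where the authors wanted no BhCG limit they said so, and for rRPLND they wrote one. If the printed limit cannot exclude anyone, that intended difference between the two groups is lost. At stake are who may be offered the operation, and which patients lie behind the rRPLND group's safety and 2-year PFS results.

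**Working it through.** The article derives no figure here, so there is none to reproduce. The check is a unit conversion followed by a comparison of sections.

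**Inputs from the article**

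- BhCG limit, rRPLND group: 50 mg/ml (4.1.1)
- AFP limit, rRPLND group: 20 ng/ml (4.1.1)
- AFP limit, Carboplatin AUC10 group: 10 ng/ml (4.1.2)
- LDH limit, rRPLND group: 1.5 times the upper limit of normal (4.1.1). This is a relative limit and cannot be compared with a mass concentration.

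**Conversion**

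- 1 mg = 1,000,000 ng, so 50 mg/ml = 50 × 1,000,000 = 50,000,000 ng/ml.
- 50 mg/ml × 1,000 ml/L = 50,000 mg/L = 50 g/L.

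**Ratio to the AFP limits**

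- 4.1.1: 50,000,000 / 20 = 2,500,000
- 4.1.2: 50,000,000 / 10 = 5,000,000

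AFP is a different analyte, so these ratios show the scale of the slip and do not measure a consequence.

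**Can a patient fail the limit?** The article gives no serum BhCG range, so the levels below are assumptions that span a wide range. Each is shown as a share of 50,000,000 ng/ml.

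| Assumed serum BhCG (ng/ml) | Share of the limit |
|---|---|
| 100 | 0.0002% |
| 10,000 | 0.02% |
| 1,000,000 | 2% |

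With an assumed plasma volume of 2.5 to 3.5 L, reaching 50 g/L would take 50 × 2.5 = 125 g to 50 × 3.5 = 175 g of circulating hormone. Over any plausible range the limit is out of reach.

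**Does another criterion supply the missing BhCG limit?** The AFP, LDH, stage and fitness criteria of 4.1.1 still apply, but none of them restricts BhCG. Nor does the good-prognosis requirement in 4.1: section 4.1.2 spells out the good-prognosis marker criteria for its seminoma group and sets no BhCG ceiling.

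**Where the error reaches.** General entry (4.1) has no BhCG cut-off of its own. Patients who are not eligible for rRPLND are offered other treatment and stay in the study (sections 2 and 5.1). The primary endpoint counts 30 recruits within 18 months (3.1). A wrong BhCG limit therefore changes membership of the rRPLND group but not the recruitment count. Section 2.2 plans at least 5 participants per de-escalation group. At that minimum, one participant admitted against the intended limit would be 1/5 = 20% of the rRPLND group.

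**The case against.** The strongest reply is that this is an evident slip of the pen in a condensed article. The lead-in and section 5.1 both tell a reader that a high BhCG is not intended, and the operational protocol may carry the right unit. Part of this stands. The restriction survives in words, and the article cannot show whether the approved protocol or the eCRF shares the error. But while it is plain that the unit is wrong, the article does not show what was meant: neither the intended unit nor whether 50 belongs to it can be recovered from the text. Nor is this a detail left to a fuller document, because the article states the criterion and states it wrongly.

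A reader might infer three stronger things that the article does not support:

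- **That sites would guess the unit differently and admit different patients.** Section 12 (Discussion) says all rRPLND procedures will be done by a small surgical team at one centre, so differing interpretations across sites are poorly supported as a route to harm.
- **That the rRPLND criteria as a whole exclude nobody.** Only the numeric BhCG limit fails to select.
- **That ineligible patients have been enrolled.** Nothing in the article shows this.

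**Conclusion.** The point holds as a unit error in an eligibility threshold. The printed BhCG limit is 50,000,000 ng/ml, 2.5 million times the AFP limit beside it. Assuming that no serum BhCG can reach 50 g/L, it excludes nobody, so the rRPLND group has in effect the same BhCG rule as the Carboplatin AUC10 group. It contradicts both its own lead-in and section 5.1.

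The consequence is confined to who may be offered rRPLND and to that group's secondary safety and PFS results. The size of any effect on those results cannot be estimated from the article.

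**What to change.** Reconcile the BhCG line in section 4.1.1 with section 5.1 and with the approved protocol v5.0. Correct the unit, and confirm that the number 50 belongs to the corrected unit. The clinical limit itself is for the investigators to state.

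The next step depends on what v5.0 and the eCRF contain:

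- **If only the article is wrong,** a published correction is enough.
- **If the approved protocol or the eCRF carries the same unit,** correct it there, correct the eCRF range, tell the sites, and recheck the BhCG eligibility of anyone already in the rRPLND group.

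The cost is a one-word correction in the first case. In the second it adds a site note, an eCRF range change and a recheck of one marker in a small group.

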#### Carboplatin AUC10 de‐escalation group‐specific inclusion criteria

4.1.2

Participants must meet the following additional inclusion criteria:Histologically confirmed seminoma (biopsy/orchidectomy).Serum tumour markers, defined by IGCCCG good prognosis criteria:AFP < 10 ng/ml and non‐rising on serial testing.Any BhCG.LDH < 2.5x ULN.
Glomerular filtration rate by EDTA clearance over 25 ml/min (a measured creatinine clearance using Cockcroft and Gault would be allowed if unable to perform EDTA clearance).Participants must be sterile or agree to use adequate contraception during the period of therapy.

### Exclusion criteria

4.2

A participant will not be eligible for inclusion in this study if any of the following criteria apply:Previous chemotherapy or radiotherapy for the disease under study.Previous or concurrent malignancy other than testicular cancer, unless treated with curative intent and with no known active disease present for ≥2 years before enrolment and felt to be at low risk for recurrence by the treating physician (for example: non‐melanoma skin cancer or lentigo maligna; breast ductal carcinoma in situ; prostatic intraepithelial neoplasia; urothelial papillary non‐invasive carcinoma or urothelial carcinoma in situ).Any condition that, in the opinion of the investigator, would interfere with evaluation of study intervention or interpretation of participant safety or study results, such as medical comorbidities impacting QoL or medical conditions or other disorders that would affect adherence to study requirements.

## METHODS

5

### Intervention

5.1

Participants will receive SOC treatments for good prognosis stage II seminoma and NSGCT or de‐escalated treatments (primary rRPLND with or without adjuvant treatment or Carboplatin AUC10) for stage II seminoma. Participants will be allocated to one of the following two cohorts based on whether the relevant de‐escalated treatment is adopted as an institutional SOC:rRPLND cohort: Participants with ipsilateral stage IIA or <3 cm IIB seminoma with negative/low for tumour markers will be offered rRPLND followed by adjuvant treatment or surveillance based on post‐operative histology as per institutional SOC.Carboplatin AUC10 cohort: Participants with stage II seminoma will be offered Carboplatin AUC10 by 3 cycles.

Participants deemed ineligible for Carboplatin AUC10 or rRPLND or those who decline this de‐escalation option will be offered either BEP or EP chemotherapy (seminoma and NSGCT) or radiotherapy with or without neoadjuvant Carboplatin AUC7 (seminoma) and will continue to be followed in the study. Chemotherapy treatment strategies and adjuvant treatments are left to the shared decision‐making between treating clinicians and participants and follow institutional SOC. The study flow diagram outlining the treatment cohorts is summarised in Figure 1.

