**Patients and Methods:**

Thirty participants with good prognosis stage II seminoma or NSGCTs will be recruited over 18 months into two cohorts: de‐escalation arm and SOC arm. The de‐escalation cohort will receive either Carboplatin AUC10 or robotic RPLND with or without adjuvant therapy depending on institutional SOC. Participants who decline or are ineligible for de‐escalation will receive SOC treatment: combination chemotherapy or radiotherapy for seminoma and combination chemotherapy for NSGCT. All participants will be followed for two years post‐treatment or until withdrawal. Data collection includes recruitment and retention rates, disease status, surgical outcomes, adverse events and patient‐reported outcomes using validated questionnaire: EORTC QLQ‐TC26, EORTC QLQ‐C30, Brief Male Sexual Function Inventory (BMSFI) and additional enquiries on anejaculation.

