### Recruitment

2.2

Thirty evaluable participants with histologically confirmed good prognosis stage II seminoma and NSGCT who have not previously received chemotherapy or radiotherapy will be enrolled from UK sites. A minimum of 5 participants will be recruited into each treatment de‐escalation group within each cohort, and a maximum of 15 patients will be recruited into the SOC groups. In the event of withdrawal, participants will not be replaced in this feasibility study. Participants will be identified in the secondary care setting via supra‐regional multi‐disciplinary team (MDT) meetings at research sites.

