### Data analysis

5.6

Summary statistics of overall participant retention within the trial until the 2‐year follow‐up visit will be presented. Full details of the analysis of all endpoints in the statistical analysis plan (SAP) will be provided, which will be finalised prior to any review or analysis of data.

*Analysis of participant populations*: The full analysis set (FAS) population and the safety set population will include all participants enrolled in the trial who received study treatment. Efficacy and safety analyses will be performed on these populations, respectively.

*HRQOL*: Summary statistics will be presented for items of each questionnaire by time point. Methods for scoring will follow the guidelines provided in the respective manuals. Further details on comparisons of questionnaires between time points and between arms will be provided in the SAP.

*PFS and OS*: The Kaplan–Meier (K‐M) methodology will be used to estimate the PFS and OS rates at 2 years, as well as the median PFS and OS for each treatment arm and for all participants. These estimates will be accompanied by 95% confidence intervals (CIs), and the K‐M curves will be plotted. The treatment effect will be evaluated by calculating the hazard ratio (HR) along with its corresponding CIs and p‐value, obtained from the Cox proportional hazards model.

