## DISCUSSION

12

There is a need for prospective trials to assess de‐escalation strategies for stage II seminoma, particularly to determine the efficacy, safety and toxicity of treatments. The lack of randomised trials in this area has led to varied institutional SOC, shaped by individual clinical experiences, making it difficult to reach an international consensus on treatment strategies.

THERATEST is the first study to prospectively evaluate standard of care treatments (multi‐cycle combination chemotherapy or external beam radiotherapy) and novel de‐escalation strategies (Carboplatin AUC10 and rRPLND with or without adjuvant chemotherapy) for good prognosis GCT. This study will contribute valuable insights to the literature by combining qualitative and quantitative data to comprehensively assess outcomes. The study will not only enhance our understanding of clinical efficacy but also provide a deeper insight into the patient‐reported outcomes, which is crucial for optimising treatment decisions within a shared decision‐making framework.

However, the study has several limitations. The relatively short follow‐up period of 2 years may be insufficient to fully assess long‐term disease relapse and treatment‐related effects. Additionally, the generalisability of the findings may be limited, as all rRPLND procedures will be performed by a small team of surgeons at a single centre. Furthermore, the lack of randomisation in treatment allocation restricts the study's ability to evaluate the feasibility of incorporating randomisation in future trials.

If successful in achieving its primary outcomes of recruitment and retention, THERATEST will lay the groundwork for a larger‐scale multicentre study, with the potential to inform broader evidence and shape future clinical guidelines. The study's findings will be crucial in addressing existing gaps in evidence and shaping the direction of future research on de‐escalation strategies for this rare cancer.

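### The planned PFS/OS treatment effect has no defined arm; read as de-escalation versus SOC, it sets seminoma alone against a mix of seminoma and NSGCT

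*Protocol article*

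**What the plan says.** **What the cohorts are.** The abstract (Patients and Methods) says that thirty participants "will be recruited over 18 months into two cohorts: de‐escalation arm and SOC arm". Section 5.1 instead has participants "allocated to one of the following two cohorts based on whether the relevant de‐escalated treatment is adopted as an institutional SOC", and names an rRPLND cohort and a Carboplatin AUC10 cohort. Section 2.2 follows the second meaning, since it speaks of a de-escalation group within each cohort. Tables 2 and 3 do too: each is the schedule for one of those cohorts, and each provides for participants who receive another institutional treatment.

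**Who can be where.** Sections 4.1.1 and 4.1.2 require confirmed seminoma for both de-escalation groups. Section 5.1 says that those who are ineligible or decline "will be offered either BEP or EP chemotherapy (seminoma and NSGCT", with radiotherapy as the alternative for seminoma. Section 2.2 sets a floor of 5 for each de-escalation group and states that "a maximum of 15 patients will be recruited into the SOC groups". It sets no quota by histology.

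**What is compared.** Section 5.6 plans Kaplan–Meier estimates of PFS and OS for each treatment arm and for all participants. It also plans a Cox hazard ratio with confidence interval and p-value as the measure of treatment effect. It does not define the arm and does not mention histology.

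**The concern.** A hazard ratio needs two defined groups, and the article supports two different pairs. They answer different questions and carry different biases.

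If the arms are de-escalation and SOC, one side is all seminoma and the other can be any mixture. The article's own Background treats histology as prognostic: it gives stage II seminoma the most favourable outcome in the good-prognosis group, with cure above 98%, against above 95% for good-prognosis metastatic disease generally. A difference produced by histology could then be reported as an effect of de-escalation. NSGCT participants carry no information about de-escalation in seminoma, because none of them can receive it.

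If the arms are rRPLND and AUC10, the treatment option follows the institution.

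Section 1 says that the findings will inform a definitive trial, so a misread contrast could carry forward.

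**Working it through.** The target of 30 is a feasibility target with no stated derivation, so there is no figure to reproduce. The check covers group composition, the possible size of the histology bias, and what a seminoma-only contrast could show.

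**1. Composition (Section 2.2).** Total 30, SOC at most 15. If the target is met, de-escalation has at least 30 − 15 = 15 participants, all seminoma. NSGCT can enter only SOC. Seminoma enters SOC only through ineligibility or refusal. With SOC at 15, the number of SOC participants with seminoma can be anything from 0 to 15.

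**2. The two readings side by side.**

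| Reading of arm | Source | What differs besides treatment |
|---|---|---|
| De-escalation v SOC | Abstract | Histology. For the rRPLND part, also stage and markers (Section 4.1.1 limits stage and markers; Section 4.1 admits any clinical stage II). Site only in part, since SOC participants come from the same sites |
| rRPLND v AUC10 | Sections 2.2 and 5.1, Tables 2 and 3 | Site: cohort is assigned by institutional practice, and the Discussion says that all rRPLND is "performed by a small team of surgeons at a single centre". The rRPLND stage and marker limits also apply |

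**3. Size of the histology bias when treatment does nothing.** Let seminoma have 2-year PFS *s* = 0.965 under any treatment. This is the figure that the Background cites for AUC10 in stage II seminoma, used here as a benchmark. Let NSGCT have PFS *n*, which the article does not give and which is assumed. With NSGCT share *f* in SOC:

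- SOC PFS = *f·n* + (1 − *f*)·*s*
- apparent HR (de-escalation v SOC) = ln(*s*) / ln(SOC PFS), the ratio of 2-year cumulative hazards

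Example: *n* = 0.90 and *f* = 0.5 give SOC PFS 0.9325, and HR = ln 0.965 / ln 0.9325 = 0.51.

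| Assumed NSGCT PFS | *f* = 0 | *f* = 0.5 | *f* = 1 |
|---|---|---|---|
| 0.95 | 1.00 | 0.82 | 0.69 |
| 0.90 | 1.00 | 0.51 | 0.34 |
| 0.85 | 1.00 | 0.37 | 0.22 |

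If NSGCT PFS equalled 0.965 the ratio would be 1.00 at every share. If it were higher, the bias would reverse.

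**4. What a seminoma-only contrast can show.** Take 15 de-escalated against *k* SOC seminoma participants, with 80% power and two-sided 5% (both assumed). The detectable standardised difference on a continuous score is (1.960 + 0.842)·√(1/15 + 1/*k*):

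- *k* = 15: 1.02 SD
- *k* = 8: 1.23 SD
- *k* = 5: 1.45 SD
- *k* = 3: 1.77 SD
- *k* = 0: no estimate

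For PFS, events are few even without restriction. At 95% PFS (the article aims for more than 95%), 30 × 0.05 = 1.5 events are expected. For two arms of 15, the chance that at least one has no event is 1 − (1 − 0.95^15)² = 71%. This is sparse data and separate from confounding, but it also argues for description rather than a test.

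**The case against.** The strongest reply is that much of this belongs to the SAP. Section 5.6 leaves full analysis details to it, including further details on "comparisons of questionnaires between time points and between arms", so restriction or adjustment by histology may be there. For HRQOL that stands: a reader might infer that a confounded HRQOL comparison is already fixed, and the article does not support this. It does not answer the point for PFS and OS, where the hazard ratio and p-value are stated in the article while the arm is undefined.

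Other stronger readings also fail:

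- **Safety.** No between-arm safety test is planned. Section 3.2 describes adverse events and complications.
- **SOC will be mostly NSGCT.** The recruitment rules permit this, but nothing predicts it. Seminoma patients who decline or are ineligible also enter SOC.
- **Site could explain any de-escalation v SOC difference.** Both cohorts include SOC participants, so site is only partly confounded there.
- **Stage separates all de-escalation from SOC.** The restriction applies to rRPLND only. The AUC10 cohort takes any stage II seminoma.
- **An all-participant PFS estimate is wrong.** The study enrols both histologies, and a pooled figure is a legitimate description. Forbidding it would be a preference.

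It is also fair to say that the body of the article uses cohort in largely one sense and that the abstract is the outlier. The wording conflict alone is a small correction. It matters because the undefined arm in Section 5.6 depends on it.

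**Conclusion.** The point holds for PFS and OS. The article fixes a treatment-effect hazard ratio without defining the arms, and both available definitions are confounded: de-escalation v SOC by histology (with stage and markers added for rRPLND), and rRPLND v AUC10 by site. The NSGCT share of SOC may be anything from 0% to 100%. With no true effect, that could move the apparent hazard ratio from 1.00 to between 0.69 and 0.22, given seminoma PFS of 96.5% and NSGCT PFS between 95% and 85%. The NSGCT values are assumptions, so the range illustrates possible bias and does not forecast it. If no SOC participant has seminoma, no adjustment can recover the contrast.

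This concerns secondary endpoints of a non-randomised feasibility study. The primary recruitment endpoint, to which NSGCT participants properly count, is unaffected. The change should be made, but the study does not depend on it.

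**What to change.** 1. Use cohort only in the Section 5.1 sense (rRPLND or Carboplatin AUC10) and correct the abstract.
2. In Section 5.6, report by treatment received in four groups: rRPLND, AUC10, SOC seminoma and SOC NSGCT.
3. Restrict any between-group PFS or OS contrast, and any HRQOL or safety comparison that the SAP adds, to seminoma. Describe NSGCT separately.
4. Label these contrasts descriptive: estimates with intervals, no p-value, and the size of the seminoma comparator stated.
5. Keep the all-participant PFS and OS estimates if wanted, shown also by histology.

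The cost is wording in the abstract, Section 5.6 and the SAP. Histology, stage and markers are already needed for eligibility, so no visits, data items or participants are added. The downside is a smaller comparator, possibly an empty one, which restriction makes visible but does not cure.
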